## **Subgroup analysis for the primary endpoint**

For the primary endpoint, subgroup analysis based on the variables listed below will be performed with the FAS. If information related to the definition of a subgroup is missing, the case will be excluded from the subgroup analysis.

- Age at time of registration (median and above/below median)
- Age at time of registration (70 and above/below 70 years)
- Sex (male/female)
- BMI at baseline (median and above/below median)
- Clinic systolic blood pressure at baseline (median and above/below median)
- Clinic systolic blood pressure at baseline (130 mmHg and above/below 130 mmHg)
- CAVI at baseline (median and above/below median)
- CAVI at baseline (9 and above/below 9)
- eGFR at time of registration (median and above/below median)
- eGFR at time of registration (45 mL/min/1.73 m^2^ and above/below 45 mL/min/1.73 m^2^)
- eGFR at time of registration (60 mL/min/1.73 m^2^ and above/below 60 mL/min/1.73 m^2^)
- UACR at time of registration (median and above/below median)
- UACR at time of enrollment (300 mg/g.cr. and above/below 300 mg/g.cr.)
- HbA1c at time of registration (median and above/below median)
- Serum potassium levels at time of registration (median and above/below median)
- LVEF at time of registration (median and above/below median)
- LVEF at time of registration (40% and above/below 40%)
- LVEF at time of registration (60% and above/below 60%)
- Duration of diabetes at time of registration (median and above/below median)
- History of hypertension at time of registration
- History of ischemic heart disease, stroke, or lower limb arteriosclerosis at time of

registration

- History of heart failure at time of registration
- Use of ACE inhibitors, ARBs, or ARNIs at baseline
- Use of concomitant SGLT2 inhibitors at baseline
- Use of concomitant GLP-1 receptor agonists at baseline
- KDIGO chronic kidney disease severity classification at time of registration (moderate,

high, very high)

## **Safety endpoints**

The following analyses will be performed with the SS. Reported adverse events will be assigned a low-level term (LLT) code using the Medical Dictionary for Regulatory Affairs, Japanese (MedDRA/J). The version of MedDRA/J used for the analysis will be the latest version at the time of database fixation.

1. Serum potassium levels (blood test parameter)
2. Descriptive statistics calculations will be conducted, and histograms will be plotted for serum potassium levels and its participant-level change by treatment group and study visit. Inferential statistics calculations will be conducted for the population-level mean and its change by treatment group and study visit. If the distribution of values deviates significantly from normal distribution, the proportional change will be described with the geometric mean and its proportional change as appropriate.
3. For serum potassium levels at each time point, analysis will be performed using MMRM with the baseline values as covariates, allocation, study visit and their interactions as fixed effects, and the patient as a random effect. The REML method will be used for the analysis with compound symmetry structure set as the covariance structure. The Kenward–Roger method will be used to calculate the degrees of freedom. To assess the treatment effect at each time point, the between-group difference in the change in the mean value using the least squares mean will be estimated using the placebo group as the reference. At each time point, the output will be the *P* value for testing the null hypothesis that the between-group ratio is 0.
4. The frequency of serum potassium levels exceeding 5.5 and 6.0 mEq/L, and falling below 3.5 mEq/L will be calculated for baseline, 4, 12, and 24 weeks after the protocol treatment initiation.
5. At 4, 12, or 24 weeks after the protocol treatment initiation, frequency of events with serum potassium exceeding 5.5 and 6.0 mEq/L, or falling below 3.5 mEq/L will be tabulated. The denominator for the tabulation will be the number of SS cases with serum potassium data after the protocol treatment initiation.
6. Hyperkalemia (adverse event)

The frequency of hyperkalemia reported as an adverse event will be tabulated. The denominator for the tabulation will be the SS.

1. Adverse events and side effects

Adverse events (TEAEs) occurring after the protocol treatment initiation will be calculated. Adverse events causally related to the study drug will be considered under side effects.

If an adverse event with the same preferred term (PT) occurred multiple times in one case, the number of occurrences will be considered as the number of events, and the number of cases will be considered separately as one case.

For all adverse events and side effects, the number of occurrences, number of cases, and incidence rate with 95% confidence intervals using the Clopper–Pearson method will be calculated for each treatment group.

The number of events, number of cases, and incidence rate will be determined by system organ class (SOC) and PT classification for each treatment group.

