### Side effects

Adverse reactions may occur; therefore, the patients will be closely monitored. If any abnormalities are identified, appropriate measures will be taken including discontinuation of the drug.

In a global phase III study (Study 16244/FIDELIO-DKD) targeting patients with CKD and type 2 diabetes administered standard treatment with ACE inhibitors or ARBs, adverse events were observed in 646/2,827 cases (22.9%) in the finerenone group and 449/2,831 cases (15.9%) in the placebo group. The main events in the finerenone and placebo groups were hyperkalemia in 286 (10.1%) and 114 (4.0%) cases, respectively; increased blood potassium in 53 (1.9%) and 22 (0.8%) cases, respectively; increased blood creatinine in 44 (1.6%) and 39 (1.4%) cases, respectively; and hypotension in 42 (1.5%) and 22 (0.8%) cases, respectively.

Serious adverse events were observed in 48 cases (1.7%) in the finerenone group and 34 cases (1.2%) in the placebo group. The main events in the finerenone and placebo groups were hyperkalemia in 24 (0.8%) and 5 (0.2%) cases, respectively; acute kidney injury in 9 (0.3%) and 6 (0.2%) cases, respectively; and hypotension in 3 (0.1%) and 2 (< 0.1%) cases, respectively.

Adverse events leading to discontinuation of the study drug were observed in 94 cases (3.3%) in the finerenone group and 59 cases (2.1%) in the placebo group. The main events in the finerenone and placebo groups were hyperkalemia in 43 (1.5%) and 12 (0.4%) cases, respectively; increased blood potassium in 10 (0.4%) and 4 (0.1%) cases, respectively; increased blood creatinine in 4 (0.1%) and 2 (< 0.1%) cases, respectively; renal disorder in 4 (0.1%) and 3 (0.1%) cases, respectively; pruritus in 4 (0.1%) and 1 case (< 0.1%), respectively; diarrhea in 3 (0.1%) and 8 (0.3%) cases, respectively; acute kidney injury in 3 (0.1%) and 3 (0.1%) cases, respectively; and rash in 3 (0.1%) and 1 case (< 0.1%), respectively.

No side effects leading to death (excluding efficacy evaluation events) were reported. (Source: Interview Form.)

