　Next, in a subanalysis of the EMPA-TROPISM trial assessing patients with HFrEF (2), after six months of administration of the SGLT2 inhibitor empagliflozin, the change in vascular stiffness assessed by aortic pulse wave velocity was –0.58 cm/s (–0.36 SD) in the empagliflozin group and +0.60 cm/s (+0.60 SD) in the placebo group, demonstrating a significant improvement with empagliflozin (estimated effect size is approximately –0.36 SD–0.60 SD = –0.96 SD), and at the same time, proteomic analysis revealed a reduction in some inflammatory biomarkers. Moreover, in the PROTECT trial (jRCT1071220089) assessing patients with type 2 diabetes, although not limited to patients with CKD, the average CAVI value was approximately 9 with an SD of approximately 1.5 (unpublished data). Using these values, –0.6SD approximately yields a CAVI of –1; thus, in this study, the CAVI value of approximately 9 is expected to lower by approximately 1. In studies focusing on patients with diabetes and the general population (3,4), the CAVI value increased by 0.5 with approximately 10 years of aging; thus, lowering the CAVI by 1 point is equivalent to delaying the progression of arterial stiffness by approximately 20 years, and is considered to be clinically significant.

　Although no studies have directly compared the clinical effects of finerenone and empagliflozin, based on previous studies, if we assume that finerenone will improve vascular stiffness similar to that by empagliflozin as observed in the EMPA-TROPISM trial, we conservatively estimated that the CAVI in SD units from baseline to 24 weeks after treatment initiation would be reduced by > –0.6 (63% of the effect detected in the EMPA-TROPISM trial, calculated as –0.96 × 0.63 = –0.6) in the finerenone group compared to that in the placebo group, and set the significance level at 5% on both sides, power at 80%, and dropout rate at 10%. Thus, the minimum number of cases required to detect a significant difference between the two groups was set at 100 (50 in each group).

References:

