### Safety analysis

Reported adverse events will be assigned a low-level term (LLT) code using the Medical Dictionary for Regulatory Affairs, Japanese (MedDRA/J). The version of MedDRA/J used for the analysis will be the latest version at the time of database fixation.

Adverse events (TEAEs) observed after protocol treatment initiation will be assessed. Adverse events identified to be causally related to the study drug will be considered side effects.

If an adverse event with the same preferred term (PT) occurred multiple times in one case, the number of occurrences will be considered as the number of events, and the number of cases will be counted separately as one case.

For all adverse events and side effects, the number of occurrences, number of cases, and incidence rate with 95% confidence intervals will be calculated for each treatment group.

The number of events, number of cases, and incidence rate will be determined by system organ class (SOC) and PT classification for each treatment group.

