**Supplementary Table S4. Safety endpoints***

| **Event** | **Finerenone**  **(*n* = 51)** | **Placebo**  **(*n* = 50)** |
| --- | --- | --- |
| Any adverse event | 8 (15.7) | 8 (16.0) |
| Any serious adverse event | 5 (9.8) | 5 (10.0) |
| Atrial fibrillation | 0 | 1 (2.0) |
| Cardiac failure | 0 | 1 (2.0) |
| Cataract traumatic | 0 | 1 (2.0) |
| Cholangitis acute | 1 (2.0) | 0 |
| COVID-19 | 1 (2.0) | 0 |
| Gastric cancer | 0 | 1 (2.0) |
| Interstitial lung disease | 1 (2.0) | 0 |
| Large intestinal polypectomy | 0 | 1 (2.0) |
| Pyelonephritis | 1 (2.0) | 0 |
| Thermal burn | 1 (2.0) | 0 |
| Documented serum potassium level† |  |  |
| >5.5 mEq/L | 0 | 0 |
| <3.5 mEq/L | 0 | 3 (6.0) |
| Investigator-reported hyperkalaemia | 1 (2.0) | 0 |
| Adverse event related to study drugs ‡ | 2 (3.9) | 1 (2.0) |
| Serious adverse event related to study drugs ‡ | 1 (2.0)§ | 0 |
| Adverse event leading to discontinuation of study drugs | 2 (3.9)¶ | 1 (2.0)‖ |

* Shown are adverse events (n [%]) that occurred after the initiation of the study drug. Serious adverse events were classified according to the preferred terms from the Medical Dictionary for Regulatory Activities.

† Data are counted based on laboratory results from weeks 4, 12, or 24.

‡ A causal relationship between any adverse event and study drug administration was based on the opinion of the reporting investigators.

§ Interstitial lung disease (interstitial pneumonia)

¶ Serious adverse events (interstitial lung disease and pyelonephritis)

‖ Non-serious adverse event (abnormal hepatic function)

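### Adverse-event incidence gets only per-arm intervals or bare frequencies, so this placebo-controlled trial plans no estimate of the finerenone-minus-placebo difference in event risk

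*Combined protocol and SAP*

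**What the plan says.** The protocol's Safety analysis section plans, for all adverse events and side effects, an "incidence rate with 95% confidence intervals will be calculated for each treatment group". The SAP's Safety endpoints section repeats this and names the method: "incidence rate with 95% confidence intervals using the Clopper–Pearson method will be calculated for each treatment group". Tables by system organ class and preferred term carry counts and incidence by arm.

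For hyperkalaemia, the SAP says: "The frequency of hyperkalemia reported as an adverse event will be tabulated". Potassium above 5.5, above 6.0 and below 3.5 mEq/L is likewise counted, by visit and over the post-baseline visits. The SAP's Frequency counting section offers Clopper–Pearson limits where needed, for single proportions only.

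The same SAP section does plan one between-arm safety analysis: an MMRM in the safety set, giving the difference between groups in mean serum potassium change at each visit.

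**The concern.** The trial randomises against placebo, and the protocol sets its safety endpoint in order to evaluate the safety of finerenone, naming hyperkalaemia. Randomisation supports the contrast between arms, yet for event incidence the plan stops at each arm separately. Elsewhere the SAP estimates a between-group effect: for CAVI, UACR, the biomarkers, vital signs, laboratory values and echocardiography. Event incidence is treated differently, and no reason is given.

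At stake is how sparse counts are read. Two percentages, or two one-sample intervals, do not state how large a difference remains compatible with the data. Equal or near-zero counts in about 50 patients per arm can be taken as showing no excess when they allow a substantial one.

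**Working it through.** **The plan's own figure.** The trial is sized for CAVI. The inputs are an effect that "would be reduced by > –0.6 (63% of the effect detected in the EMPA-TROPISM trial", in SD units, and the plan "set the significance level at 5% on both sides, power at 80%, and dropout rate at 10"%.

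- Normal approximation: n per arm = 2(1.96 + 0.8416)² / 0.6² = 43.6, so 44. Then 44/0.9 = 48.9, so 49 per arm, or 98 in total.
- t distribution: 45 per arm (power 80.4%). Then 45/0.9 = 50 per arm, or 100 in total, as stated.

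The documents give no power or precision figure for adverse events.

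**Cited event rates.** The protocol's Side effects section reports "hyperkalemia in 286 (10.1%) and 114 (4.0%) cases, respectively" in the first phase III trial, an excess of 10.1 − 4.0 = 6.1 points. The second had 5.7% and 2.7%, an excess of 3.0 points. The documents do not give follow-up for either trial, so these rates are a benchmark and not a 24-week forecast.

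**What a between-arm interval would do at those rates.** Every pair of binomial counts with 50 per arm was enumerated. Each was given Clopper–Pearson intervals per arm and a Newcombe interval for the difference.

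| Share of trials | 10.1% v 4.0% | 5.7% v 2.7% |
|---|---|---|
| Newcombe interval above 0 | 16.1% | 4.8% |
| Newcombe above 0 while arm intervals overlap | 14.2% | 4.6% |
| Arm intervals separate | 2.0% | 0.2% |
| Finerenone count no higher than placebo | 15.4% | 31.0% |

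The usual normal-approximation formula for two proportions (pooled variance under the null) gives power of 21.9% and 11.2% at 50 per arm. Power of 80% would need 276 and 701 per arm. The sample size is therefore the main limit.

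**What it would show with the reported counts.** For arm proportions p₁ and p₂, with Wilson limits (l₁, u₁) and (l₂, u₂) and d = p₁ − p₂, the Newcombe limits are

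lower = d − √[(p₁ − l₁)² + (u₂ − p₂)²]

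upper = d + √[(u₁ − p₁)² + (p₂ − l₂)²]

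*Hyperkalaemia.* Supplementary Table S4 gives "Investigator-reported hyperkalaemia | 1 (2.0) | 0", that is 1/51 against 0/50. The Wilson limits are 0.35 to 10.30% and 0 to 7.13%, and d = 1.96.

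- Lower: 1.96 − √(1.61² + 7.13²) = 1.96 − 7.31 = −5.35
- Upper: 1.96 + √(8.34² + 0²) = 10.30

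The difference is 2.0 points (−5.4 to 10.3). This excludes neither the 6.1-point nor the 3.0-point excess.

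*Any adverse event.* The counts are 8/51 against 8/50. The Wilson limits are 8.17 to 28.01% and 8.34 to 28.51%, and d = 15.69 − 16.00 = −0.31.

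- Lower: −0.31 − √(7.52² + 12.51²) = −0.31 − 14.60 = −14.91
- Upper: −0.31 + √(12.32² + 7.66²) = −0.31 + 14.51 = 14.20

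*Any serious adverse event.* The counts are 5/51 against 5/50. The Wilson limits are 4.26 to 20.98% and 4.35 to 21.36%, and d = 9.80 − 10.00 = −0.20.

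- Lower: −0.20 − √(5.54² + 11.36²) = −0.20 − 12.64 = −12.84
- Upper: −0.20 + √(11.18² + 5.65²) = −0.20 + 12.53 = 12.33

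*Potassium above 5.5 mEq/L.* The counts are 0/51 against 0/50, so d = 0. Each limit is then set by one Wilson upper bound (7.13% placebo, 7.00% finerenone), which gives −7.1 to 7.0 points.

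**The case against.** The strongest reply is that descriptive safety tables are a defensible choice in a 100-patient trial with a surrogate primary endpoint, and that protocol and SAP agree on it. Several parts of this stand.

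- **Potassium is compared between arms.** A reader might infer that hyperkalaemia safety is left wholly to comparison by eye. It is not. The planned MMRM is a more sensitive measure of potassium shift than event counts, and Supplementary Table S2 reports a difference of 0.3 mEq/L (0.1 to 0.4) at week 4. What remains is that a difference in means does not estimate the risk of an event.
- **There is no overlap rule.** A reader might infer that the plan judges safety by whether the arm intervals overlap, and so would hide a real excess. Neither document says so, and Table S4 prints no arm intervals.
- **Power stays low.** A reader might infer that a between-arm interval would detect the excess. At the cited rates it would lie above 0 in only 16.1% or 4.8% of trials.
- **The arm interval already carries some of the message.** With no placebo events, the finerenone Clopper–Pearson upper limit for 1/51 is 10.4%, close to the 10.3-point upper limit for the difference. That closeness depends on the zero placebo count. It does not carry over to 8/51 against 8/50. The SAP's hyperkalaemia item itself promises only a frequency.

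A reader can also derive a risk difference from the published counts. That is true, but it leaves the trial's own safety estimate to the reader.

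**Conclusion.** The gap is real and modest. For adverse-event incidence, including hyperkalaemia and the potassium thresholds, the plan yields no estimate of the difference between finerenone and placebo. No stated figure is wrong, and the primary analysis is untouched.

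The gain from closing it is in estimation, not detection. Reported hyperkalaemia leaves room for an excess of up to about 10 points, and the near-equal adverse-event percentages leave room for about 14 points either way. The documents do not support saying that the plan would miss an excess which an interval would have found, because sample size is the main limit.

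The event-specific intervals rest only on the Table S4 counts. The percentages of trials assume 50 per arm and that the cited phase III rates apply over 24 weeks, which the documents do not establish.

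**What to change.** In the SAP's Safety endpoints section, add the finerenone-minus-placebo risk difference with a 95% Newcombe (or Miettinen–Nurminen) interval in the safety set, for:

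- any adverse event, any serious adverse event and any side effect;
- hyperkalaemia reported as an adverse event;
- potassium above 5.5, above 6.0 and below 3.5 mEq/L at any post-baseline visit, with the denominator the SAP already defines.

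Present these as descriptive estimates without P values. Keep the per-arm intervals and the potassium MMRM. If the analysis is added after database lock, label it as not prespecified.

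The cost is one SAP sentence, a few lines of R and one table column, using data already collected. The downside is wide intervals, unadjusted for multiplicity.

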# **Statistical analysis and tabulation** **software**

| OS | Microsoft Windows 11 or later |
| --- | --- |
| Statistical analysis software | R4.2.0 or later |
| Representative software | R and Microsoft Excel |

# **Amendment**

|  | **(Before change) September 30, 2024** |  | **(After change) October 31, 2024** | **Reason for change** |
| --- | --- | --- | --- | --- |
| P.1 | Created on September 30, 2024 (Version 1.0) | P.1 | Created on October 31, 2024 (Version 1.1) | Revision |
| P.2 | **Creation/Revision history** | P.2 | **Creation/Revision history**  (2nd line in the table)  1.1 October 31, 2024 Added description on handling of CAVI data, [name] | Revision |
| P.5 | **1.2 Definitions of abbreviations** | P.5 | **1.2 Definitions of abbreviations**  (1st line in the table)  ABI ankle brachial index, Ankle-brachial index | This information was needed owing to the revisions |
| P.10 |  | P.10 | **5.4 CAVI data handling**  CAVI data with low ABI values (≤ 0.9) will not be used in the tabulation and analysis owing to its limited reliability. If CAVI data from both sides are available, they will be averaged and used for tabulation and analysis. If CAVI data from only one side are available, that CAVI data will be used for tabulation and analysis. | CAVI data handling was determined based on discussions with experts in CAVI assessment |

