# **Endpoints**

## **Primary endpoint**

Change in CAVI at 24 weeks after protocol treatment initiation as compared to that at baseline

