## **Other endpoints**

1. Changes from baseline in vital signs (weight, body mass index (BMI), estimated extracellular volume (eEV), blood pressure, pulse pressure, and pulse rate in the clinic, in addition to blood pressure, pulse pressure, and pulse rate at home) at 4, 12, and 24 weeks after the protocol treatment initiation
2. Changes from baseline in blood test indices (serum creatinine, estimated glomerular filtration rate (eGFR), serum cystatin C*, serum potassium, Hemoglobin A1c (HbA1c*), plasma (or serum) aldosterone concentration**, plasma (or serum) renin activity or concentration**) at 4, 12, and 24 weeks after the protocol treatment initiation (*evaluated only at baseline, and 12, and 24 weeks; **evaluated only at baseline and 24 weeks)
3. Changes from baseline in augmentation index (AI) and % mean arterial pressure at 24 weeks after the protocol treatment initiations
4. Changes from baseline in cardiac function indices (left ventricular ejection fraction (LVEF), septal e', lateral e', E, E/e'*, left ventricular mass index (LVMI), left atrial dimension (LAD), left atrial volume index (LAVI)) assessed by echocardiography 24 weeks after the protocol treatment initiation

*Three types of E/e' will be evaluated including E/septal e', E/lateral e', and E/average (septal e', lateral e')**

** average (septal e', lateral e') = (septal e' + lateral e')/2. If septal e' is missing, average (septal e', lateral e') = lateral e'. If lateral e' is missing, average (septal e', lateral e') = septal e'. If both are missing, average (septal e', lateral e') is also missing.

1. Changes in abundance of up to 181 proteins comprehensively analyzed by proteomic analysis (Olink Target 96 CVD III analysis, Olink Target 96 Inflammation analysis), 24 weeks after the protocol treatment initiation as compared to that at baseline (exploratory endpoint)

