# **Data handling**

## **Handling missing data**

Unless otherwise specified, missing values will be treated as missing values and will not be imputed with other data or used in tabulations or descriptive statistics calculations.

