## **Defining calculation items**

The change in endpoint A (participant-level) at a certain time point, t, is defined as follows:

Change in endpoint A = Endpoint A(t) - Endpoint A(baseline)

The proportional change (participant-level) of endpoint A at a certain time point, t, is defined as follows:

Proportional change of endpoint A = Endpoint A(t) / Endpoint A(baseline)

The change in the mean value of endpoint A (population-level) at a certain time point, t, is defined as follows:

Change in the mean value of endpoint A(t) = mean value of endpoint A(t) - mean value of endpoint A(baseline)

The proportional change of the geometric mean of endpoint A (population-level) at a certain time point, t, is defined as follows:

Proportional change in geometric mean of endpoint A(t) = geometric mean of endpoint A(t)/geometric mean of endpoint A(baseline)

= exp (ln (endpoint A) mean(t) - ln (endpoint A) mean(baseline))

= exp (ln (endpoint A) mean change (t))

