## **Analysis of the primary endpoint**

The following analysis will be performed on the FAS as the primary analysis. Furthermore, an analysis will be conducted using the PPS to confirm the robustness of the results.

1. Descriptive statistics calculations will be conducted, and histograms will be plotted to assess CAVI and its participant-level change and proportional change by treatment group and study visit. Inferential statistics calculations will be used to estimate CAVI mean and change, and geometric mean and proportional change at population-level by treatment group and study visit.
2. As the primary analysis for the primary endpoint, change in CAVI at 24 weeks will be analyzed using a linear regression model with baseline values as covariates and allocation as fixed effects. To assess treatment effect, the between-group difference in CAVI change using the least squares mean at 24 weeks will be estimated using the placebo group as a reference. The output will be the *P* value of the test for the null hypothesis that the between-group difference in change is 0. Moreover, the presence or absence of a treatment effect will be determined using the criteria of a two-sided *P* value of < 0.05.
3. As a supplementary analysis for the primary endpoint, change in logarithmic CAVI at 24 weeks will be analyzed using a linear regression model with logarithmic baseline values as covariates and allocation as fixed effects. To assess treatment effect, the between-group ratio of the proportional change in CAVI geometric mean using the least squares mean at 24 weeks will be estimated using the placebo group as a reference. The output will be the *P* value of the test for the null hypothesis that the between-group ratio is 1.

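### SAP 5.4 does not require the same leg(s) at baseline and week 24, so part of a left-right CAVI gap can be recorded as change in the primary endpoint: avoidable noise, probably small

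*Combined protocol and SAP*

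**What the plan says.** The rule is in SAP section 5.4, CAVI data handling, in the after-change column of the Amendment table (v1.1, October 31, 2024). I take it as the text in force. It has three parts:

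- Exclusion: "CAVI data with low ABI values (≤ 0.9) will not be used in the tabulation and analysis owing to its limited reliability".
- Both legs: "If CAVI data from both sides are available, they will be averaged and used for tabulation and analysis".
- One leg: "If CAVI data from only one side are available, that CAVI data will be used for tabulation and analysis".

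The second and third parts only make sense if evaluability is judged leg by leg.

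Under Defining calculation items, the SAP sets a participant's change as the value at time t minus the value at baseline, with no condition on side. Under Handling missing data, "missing values will be treated as missing values and will not be imputed with other data", and matching of sides is not mentioned. The primary analysis reads: "change in CAVI at 24 weeks will be analyzed using a linear regression model with baseline values as covariates and allocation as fixed effects". Its only companions are a per-protocol repeat and a log-scale version. Addressing multiplicity of tests rests the efficacy conclusion on this one analysis in the FAS.

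**The concern.** A change score should compare like with like. As written, a patient may have the mean of two legs at baseline and one leg at week 24, or the left leg at one visit and the right at the other. A fixed difference between that patient's legs is then recorded as change over 24 weeks.

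The situation is foreseeable. Lower-limb arteriosclerosis obliterans is a recorded background item in the protocol and is not among the exclusion criteria, so some legs near or below an ABI of 0.9 can be expected. A leg near the cut-off can cross it between visits, and a reading can be missing on one side.

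The protocol's Table 1 schedules CAVI only at baseline and week 24, so no other visit can dilute a mismatch. The per-protocol and log-scale analyses use the same constructed value, so neither would reveal one. What is at stake is precision in the endpoint that decides the trial, plus a possible difference between arms if leg availability were related to treatment.

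**Working it through.** **Inputs from the documents.** Protocol, Sample size: effect 0.6 SD, two-sided 5%, power 80%, dropout 10%, CAVI mean about 9 and SD about 1.5. Protocol, Randomization procedure: 1:1 allocation.

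**Inputs assumed, because the documents do not give them.** Share of patients with a side mismatch, f: 5–20%. SD of the left-right gap across patients, d: 0.2–1.0, with mean gap zero. SD of change: 1.5. The protocol gives 1.5 for CAVI itself, so using it for change is an assumption; 0.8 is tried as an alternative.

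**1. The plan's sample size reproduces.** A two-sample t-test with effect 0.6 SD needs 44.6, so 45 per arm. 45/0.9 = 50 per arm, 100 in total. Power with 45 evaluable per arm is 80.4%. The sample size is not in dispute.

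**2. One patient.** Let D be left minus right.
- Two legs at one visit and one at the other: artefact ±D/2.
- One leg at one visit and the other leg at the other: artefact ±D.

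With assumed legs of 9.5 and 8.5 and no true change, the two-leg mean is 9.0. Both legs then left only gives +0.5. Both then right only gives −0.5. Left then right gives −1.0. Against an SD of 1.5, 0.5 is one third of an SD.

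**3. The trial.** Variance of change becomes SD² + f·d²/4 (two legs against one) or SD² + f·d² (leg switch). The effect is held at 0.6 × 1.5 = 0.9, with 45 per arm:

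| f | d | Two against one: SD, power | Leg switch: SD, power |
|---|---|---|---|
| 5% | 0.2 | 1.5002, 80.4% | 1.5007, 80.3% |
| 10% | 0.5 | 1.5021, 80.3% | 1.5083, 79.9% |
| 20% | 1.0 | 1.5166, 79.5% | 1.5652, 77.0% |

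In the last row, 2.25 + 0.20 × 1.0/4 = 2.30, with square root 1.5166; and 2.25 + 0.20 × 1.0 = 2.45, with square root 1.5652. Restoring 80% power in the worst of these cells takes 110 patients instead of 100.

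With SD of change 0.8 and the effect still 0.6 SD (0.48), the worst cell (20%, gap SD 1.0, every mismatch a leg switch) has SD √(0.64 + 0.20) = 0.9165, power 69.0% and N = 132. With two legs against one, the same cell has power 77.4%.

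**4. False positives.** The baseline-adjusted model was simulated under no effect: 45 per arm, SD 1.5, baseline to week 24 correlation 0.85 (assumed), 5,000 runs, two-against-one artefact at week 24. With 10% affected in both arms, the rejection rate was 4.8% (gap SD 0.5) and 5.3% (gap SD 1.0), against 4.6% with no mismatch. Monte Carlo error is about ±0.6 points.

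**5. If mismatches did differ by arm.** Suppose 5–10% of one arm, and none of the other, carry an artefact of 0.5 in the same direction. The group difference moves by 0.05 × 0.5 = 0.025 to 0.10 × 0.5 = 0.05. The SE is 1.5 × √(2/45) = 0.32, so the shift is 0.08–0.16 SE. With an assumed residual SD of 0.9, the SE is 0.19 and the shift 0.13–0.26 SE.

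**The case against.** The strongest reply is that this is a gap in wording with little consequence. The rule is the same in both arms, the trial is double-blind, and no part of the documents links treatment to ABI. The calculations support this: the type I error stays near 5%, and at SD 1.5 the two-against-one case costs less than one point of power. The larger losses need leg switching, a high share affected or a smaller SD of change. All of that stands, and it sets the severity.

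The SAP also does not state that legs are chosen separately at each visit. That is the natural reading of a rule with no cross-visit condition, but it is an inference. CAVI measurement follows a test guide in an appendix that is not among the documents.

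A reader might go further and infer that losing a low-ABI leg at week 24 shifts CAVI in a known direction and so biases the treatment comparison. The documents do not support this: section 5.4 speaks only of limited reliability and gives no direction.

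A reader might also conclude that week-24 values with low ABI belong in the primary analysis, because week-24 ABI is measured after randomization. The point about post-randomization selection is fair. But that remedy would set aside a reliability judgement that the sponsor records as based on discussion with CAVI experts, so it belongs in a sensitivity analysis.

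**Conclusion.** The gap is real. A plan followed exactly can record half or all of a left-right difference as change in the only endpoint that decides efficacy. It is mainly avoidable noise. Between-arm bias would need leg availability to differ by arm, and nothing in the documents shows that it does.

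The trial-level effect is probably small: power of 77.0–80.4% instead of 80.4%, under assumed shares of 5–20%, a gap SD of 0.2–1.0 and an SD of change of 1.5. The 69.0% figure needs the most adverse combination tried. None of these inputs can be checked in the documents.

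It does not follow that the trial's result is wrong. Setting one patient's artefact beside the planned group difference of 0.9 would also mislead, because it mixes individual and group scales. Severity: minor. The change is worth making because it is cheap and concerns the primary endpoint.

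**What to change.** In SAP 5.4:

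1. Compute baseline CAVI, week-24 CAVI and change from the same leg or legs, namely those with CAVI recorded and ABI above 0.9 at both visits.
2. Treat a patient with no common leg as missing under Handling missing data.
3. Report by arm how many patients have a side mismatch, separating two legs against one from a leg switch.
4. Keep the present 5.4 rule as a sensitivity analysis.
5. Because step 1 still selects on week-24 ABI, add a sensitivity analysis that selects legs on baseline ABI only.

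Optionally, apply the same principle to average e' under Other endpoints, where one component may stand in for the mean at one visit only. This is a lesser matter: echocardiography is optional and e' does not decide the trial.

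The cost is a few sentences and a small programming change, since side-level CAVI and ABI are already needed for the present rule. Some patients will contribute one leg instead of two. The only additional patients lost from the primary analysis are those whose single evaluable leg differs between visits; a patient with no evaluable leg at a visit is already missing.

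The supplementary tables in the same file already report results, so for this trial the same-leg analysis would have to be labelled post hoc. If the count in step 3 is zero, one sentence closes the matter.
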